### Withdrawal

Participants may withdraw from the study for any reason at any time, without penalty.

### Dropouts

All dropouts and attrition during the course of the study will be monitored and the respective reasons for withdrawal will be recorded. All randomized participants will be included in the analysis independent of whether they complete the intervention or not (intention-to-treat principles).

### Sample size

Based on a previous study [11], the sample size was calculated to detect a difference of 2 points on the pain intensity measured by the 11-point pain NRS. In our study, the sample size was calculated using the program G*Power 3 3.1. 9.2, with an estimated standard deviation of 1.47 points [30], a moderate effect size (0.35) [31], a statistical power of 80% (1 β error probability), and an α error level probability of 0.05. The study will require 105 individuals. However, an extra 20% of participants will be added in order to increase the power. Thus, this study will therefore require a total of 125 participants, with 25 in each group.

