### Study objectives

This study aims to evaluate the clinical efficacy of EA in older adults with LBP.

Our primary study goal is to screen a dominant EA frequency on pain management and its secondary outcomes in EA groups.

Our second goal is to determine whether EA is a more effective treatment than acupuncture (control) and placebo in older people with chronic LBP, in a one-year randomized controlled trial (RCT) (NCT03802045).

Our third goal is to determine the long-term effect of the EA, acupuncture, and placebo on LBP in older adults after six months and one year at the end of treatment.

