### Statistical analysis

The analysis of the data will follow the intention-to-treat principles. The normality of the data distribution will be assessed by the Kolmogorov–Smirnov test. The Pearson test will be used for correlations between variables that present a normal distribution, and the Spearman test will be adopted for correlations between variables that present a non-normal distribution.

The data will also be analyzed using the ANCOVA mixed model, considering age, gender, body mass index, and RMQ score as the covariates. The differences between groups for the primary and secondary outcome measurements will be analyzed using the linear mixed models (random intercepts and fixed coefficients), which incorporated terms for treatment, time, and the treatment by time interactions. The Bonferroni post hoc test will be used to control the overall type I error rate at the prespecified 5% level. Furthermore, in order to verify the magnitude of the differences between the interventions, the effect size (Cohen’s d) will be calculated [30].

All the analyses will be carried out using the SPSS program (IBM Corp., Armonk, NY, USA) for Windows, V.19.0. The confidence interval will be established at 95%, and the significance level will be set at 5%.

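### The sample-size inputs (2 points, SD 1.47, effect size 0.35) are incompatible, and 105 matches a five-arm omnibus test rather than the comparison the primary goal needs

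*Protocol article*

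**What the plan says.** The Sample size section names the target first: "the sample size was calculated to detect a difference of 2 points on the pain intensity measured by the 11-point pain NRS". It then lists the inputs given to G*Power, "with an estimated standard deviation of 1.47 points [30], a moderate effect size (0.35) [31], a statistical power of 80" per cent, with an α of 0.05, and arrives at 105. Neither the test nor the effect-size index is named. It continues: "However, an extra 20% of participants will be added in order to increase the power", which brings the total to 125, or 25 in each of five arms.

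Two other sections show what the number has to serve. Under Study objectives: "Our primary study goal is to screen a dominant EA frequency on pain management and its secondary outcomes in EA groups". Comparing EA with the acupuncture control and with placebo is the second goal. Under Statistical analysis, the outcomes go into linear mixed models with treatment, time and their interaction, followed by multiplicity control: "The Bonferroni post hoc test will be used to control the overall type I error rate at the prespecified 5% level".

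**The concern.** A difference, an SD and an effect size are not three free inputs. The first two constrain the third, and here the third lies outside what they allow. A reader who takes the paragraph at face value believes that 105 people give 80% power for 2 points at SD 1.47, but that pair of figures did not produce 105.

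The number also appears to come from a test of any difference among five arms. That test can be significant solely because the placebo arm differs, and it does not say which frequency is best. The paragraph gives no power for an EA-versus-EA contrast. If the trial finds no difference between frequencies, a reader cannot tell from the plan what size of difference was reasonably excluded.

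**Working it through.** **Inputs from the Sample size section.** Difference 2 points; SD 1.47; effect size 0.35; power 80%; α 0.05; N 105, then 125; five equal arms.

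**1. Reproduce 105.** One-way ANOVA F test with k = 5 and f = 0.35: noncentrality λ = f² × N, with 4 and N − 5 degrees of freedom.
- The smallest N for 80% power is 103, which rounds up to 105 for equal arms.
- At N = 105, λ = 0.1225 × 105 = 12.9 and power is 81.2%. At N = 125, λ = 15.3 and power is 88.5%.
- An ANCOVA F test with one or four covariates also gives 105.
- Neither 2 points nor 1.47 enters this calculation.

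**2. Derive f from 2 points and SD 1.47.** d = 2/1.47 = 1.36. With f = σ_m/SD, where σ_m is the SD of the five arm means, a 2-point range gives:

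| Pattern of five means | f | Total N for 80% (equal arms) |
|---|---|---|
| Two extremes, three midway | 1.36 × √(1/10) = 0.43 | 70 |
| Equally spaced | 1.36 × √(1/8) = 0.48 | 60 |
| One arm apart | 1.36 × 2/5 = 0.54 | 50 |
| Three arms against two | 1.36 × √24/10 = 0.67 | 35 |

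The first row is the minimum, so no set of means with two arms 2 points apart gives f = 0.35.

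**3. Run it backwards.** f = 0.35 at SD 1.47 means σ_m = 0.35 × 1.47 = 0.5145. The range of means is then 0.5145 × √10 = 1.63 (two extremes), 0.5145 × 2.5 = 1.29 (one arm apart) or 0.5145 × 10/√24 = 1.05 (three against two). To make f = 0.35 fit 2 points, the SD would have to be 1.81 to 2.80.

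**4. Try other readings of 0.35.** As Cohen's d it is 0.35 × 1.47 = 0.51 points and needs 130 per arm. As f² it gives f = √0.35 = 0.59, which is compatible with 2 points, but the five-arm test then needs 40 in total. Neither gives 105.

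**5. What 25 per arm delivers for a pairwise contrast.** Noncentral t with noncentrality (difference/SD) × √(25/2) and 120 pooled degrees of freedom (125 − 5), two-sided. The Statistical analysis section does not define the Bonferroni family, so both candidates are shown: the 3 EA pairs (α = 0.05/3) and all 10 pairs (α = 0.005). SDs of 2.0 and 2.5 are assumptions.

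| Difference, SD | 3 pairs | 10 pairs |
|---|---|---|
| 2 points, 1.47 | 99% | 97% |
| 2 points, 2.0 (assumed) | 86% | 75% |
| 2 points, 2.5 (assumed) | 66% | 49% |
| Difference with 80% power, SD 1.47 | 1.36 points | 1.54 points |

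The last row is the standardised difference with 80% power times the SD: 0.926 × 1.47 and 1.049 × 1.47.

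**6. The extra 20.** 125 − 105 = 20, and 20/125 = 16%. If losses bring the trial back to 105, five-arm power at f = 0.35 returns from 88% to 81%.

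**The case against.** The strongest reply is that the inconsistency errs on the safe side. On the stated 2 points and SD 1.47, the trial is larger than it needs to be, and f = 0.35 is the conservative input. That stands. A reader might infer from the mismatch that the primary goal is underpowered, and the documents do not support that. Carrying f = 0.35 over to the three EA arms gives 76% power at 75 people, but in three arms at SD 1.47 that f is a range of only about 1.09 to 1.26 points, which the protocol never names as a target. With 2 points between the extreme EA arms, f is at least 1.36/√6 = 0.56 and the three-arm F test has about 99% power. Nor does the protocol give an expected difference between frequencies, so no smaller difference can be called the realistic one.

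A second reply is that the test is unnamed and an omnibus test is not foreign to the plan. This stands in part. The one-way F test is an inference, ANCOVA gives the same number, and a mixed model also yields omnibus treatment and interaction tests. But an omnibus test still does not say which frequency is best, and it is not the Bonferroni comparison.

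The gap between 105 × 1.2 = 126 and the stated 125 is rounding to five equal arms and carries no weight.

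None of these replies makes 2 points, 1.47 and 0.35 agree.

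**Conclusion.** The sample-size paragraph is wrong as written. At the stated SD, 2 points means f of 0.43 to 0.67, not 0.35. The stated 105 is the size for f = 0.35, a spread of 1.05 to 1.63 points, in what appears to be a five-arm omnibus F test. That test does not answer the primary goal and is not the planned pairwise inference.

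The fault lies in the justification, not in the number of patients. At 2 points and SD 1.47, 25 per arm gives well over 80% power for every pairwise contrast under either Bonferroni family. Pairwise power for 2 points falls below 80% only if the SD is larger than stated: at an assumed 2.0 with 10 pairs, or at an assumed 2.5 with either family.

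The conclusion rests on equal arms, full data, a single-time comparison without the gain from covariates or repeated measures, and the inferred identity of the test. The arithmetic conflict between 2, 1.47 and 0.35 as f does not depend on that last inference. The sources cited for 1.47 and 0.35 were not available, so which input was intended is left open.

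**What to change.** Keep 125 and rewrite the Sample size paragraph.

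- Name the test and the effect-size index behind 105, and remove the statement that 105 was calculated to detect 2 points at SD 1.47.
- State what 25 per arm delivers with no losses. Five-arm F test at f = 0.35: 88%. EA-versus-EA contrast with Bonferroni over 3 pairs: 99% for 2 points at SD 1.47, and 80% for 1.36 points. Over all 10 pairs: 97% and 1.54 points. Say which family applies.
- Add the rows for SD 2.0 (86% and 75%) and SD 2.5 (66% and 49%), labelled as assumptions.
- Say that the 20 extra participants cannot both raise power and absorb losses. Counted as a reserve against the 105 of the five-arm test, they cover 16% loss, at which point power is 81%.

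The cost is one reworded paragraph, with some figures less favourable than the present text suggests. No patients are added and the design does not change.

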### Statistical analysis

The analysis of the data will follow the intention-to-treat principles. The normality of the data distribution will be assessed by the Kolmogorov–Smirnov test. The Pearson test will be used for correlations between variables that present a normal distribution, and the Spearman test will be adopted for correlations between variables that present a non-normal distribution.

The data will also be analyzed using the ANCOVA mixed model, considering age, gender, body mass index, and RMQ score as the covariates. The differences between groups for the primary and secondary outcome measurements will be analyzed using the linear mixed models (random intercepts and fixed coefficients), which incorporated terms for treatment, time, and the treatment by time interactions. The Bonferroni post hoc test will be used to control the overall type I error rate at the prespecified 5% level. Furthermore, in order to verify the magnitude of the differences between the interventions, the effect size (Cohen’s d) will be calculated [30].

All the analyses will be carried out using the SPSS program (IBM Corp., Armonk, NY, USA) for Windows, V.19.0. The confidence interval will be established at 95%, and the significance level will be set at 5%.

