### Outcome measures

Four stages of evaluations will be performed: (1) before the start of treatment; (2) immediately after the end of treatment (five weeks); (3) at six months; and (4) one year after the final treatment. The evaluators will be trained in advance.

The primary clinical outcome will be pain intensity. The secondary outcomes will include quality of pain, physical functioning, perception of overall effect, emotional functionality, patient satisfaction, and psychosocial factors. All the scales and questionnaires have been translated into Brazilian Portuguese, with the exception of the visual analog scale for the assessment of anxiety, and their properties clinimetrically tested [13–16].

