### Primary outcomes

#### Pain intensity

##### Numerical rating scale (NRS)

The NRS is an 11-point scale ranging from 0 (no pain) to 10 (worst possible pain). Participants will be asked to rate their average pain levels in the 24 h before the assessment [17].

The pressure pain threshold (PPT) will be measured using a pressure algometer (EMG System, Brazil). The assessed region will be marked with a tape measure and a dermatographic pencil. Two points will be marked bilaterally: 5 cm to the right and left of the spinous process of L3 and L5. A control point will be marked on the anterior tibial muscle of the right leg, 5 cm lateral to the tuberosity of the tibia [18]. The circular tip of the algometer will be positioned perpendicular to the participant’s skin and gradually pressed until the participant reports that the pressure has become painful and unbearable. Three measurements will be taken at each point with an interval of 1 min. Finally, the arithmetic mean will be used to define the pressure pain threshold [18].

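### The protocol claims overall 5% error control, but two instruments sit under the primary heading, no primary time is named, and the Bonferroni family is not stated

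*Protocol article*

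**What the plan says.** All references are to the protocol article.

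- **Outcome measures** names one concept: "The primary clinical outcome will be pain intensity". It sets three post-baseline assessments (end of treatment at five weeks, six months, one year) and does not say which one is primary.
- **Primary outcomes, Pain intensity** describes the NRS and then, under the same heading: "The pressure pain threshold (PPT) will be measured using a pressure algometer". On the sites it says: "Two points will be marked bilaterally: 5 cm to the right and left of the spinous process of L3 and L5". That is four lumbar points, and a tibial control point makes five. Three readings are taken at each point and a mean defines the threshold. Whether that mean is per point or across points is not clear.
- **Study objectives** puts the frequency question first: "Our primary study goal is to screen a dominant EA frequency on pain management and its secondary outcomes in EA groups". EA against acupuncture and placebo is the second goal; the six-month and one-year effects are the third.
- **Sample size** uses the NRS only.
- **Statistical analysis** fits one mixed model (treatment, time and their interaction) to primary and secondary outcomes alike, and adds: "The Bonferroni post hoc test will be used to control the overall type I error rate at the prespecified 5% level".

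**The concern.** An overall error rate has meaning only for a stated set of tests. Here the set could be the 10 arm pairs for one outcome at one time, those pairs over three times, or those pairs over three times and two or more instruments. A Bonferroni post hoc test after a mixed model ordinarily adjusts comparisons within that model. It does not reach a second model fitted to another instrument, and often it does not reach across time points either. With two instruments under the primary heading and no primary time, a significant pair on either instrument at any assessment could be presented as a primary result under a 5% claim that does not cover it.

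The frequency goal has the same gap. The pairwise comparisons include the three EA arms, but no contrast, endpoint or time is tied to that goal.

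**Working it through.** **1. The plan's own figure.** A one-way ANOVA with five groups, f = 0.35, α = 0.05 and power 80% needs N = 103, or 105 when balanced (power 81.2%). This reproduces the stated 105. The sizing is therefore one five-group F test on one outcome, and it makes no allowance for several primary measures or times.

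**2. Inputs for the error rate.** Five arms give 5 × 4 / 2 = 10 pairs, of which 3 are EA versus EA. There are 25 participants per arm, three post-baseline times and α = 0.05 (two-sided assumed). Usual reading of Bonferroni: each pair is tested at 0.05 / 10 = 0.005 within each outcome and time.

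**3. Upper limits that need no correlation** (number of tests × 0.005):

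| Looks | Any of 10 pairs | EA-versus-EA pairs only |
|---|---|---|
| NRS, one time | 10 × 0.005 = 5% | 3 × 0.005 = 1.5% |
| NRS, three times | 3 × 5% = 15% | 3 × 1.5% = 4.5% |
| NRS + one PPT value, three times | 6 × 5% = 30% | 6 × 1.5% = 9% |

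If the looks were independent and each used exactly 5%, the any-pair figures would be 1 − 0.95³ = 14.3% and 1 − 0.95⁶ = 26.5%.

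**4. Simulation under no effect.** 25 per arm, pooled-variance pairwise t tests at 0.005. The correlations are assumptions, since the article gives none: 0.3 to 0.7 between times, 0 to 0.3 between NRS and PPT.

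| Looks | Any of 10 pairs | EA-versus-EA pairs only |
|---|---|---|
| NRS, one time | about 4% | about 1.2–1.6% |
| NRS, three times | about 10–11% (9–12% at the extremes) | about 3–4% |
| NRS + one PPT value, three times | about 17–21% | about 6–8% |

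**5. If Bonferroni covered everything.** Two measures × three times × 10 pairs = 60 tests at 0.05 / 60 = 0.00083, and the overall rate would be at most 5%. The article does not say that this is intended.

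**6. Power at the stated inputs.** d = 2 / 1.47 = 1.36; noncentrality 1.36 × √(25/2) = 4.81; 120 degrees of freedom. Power for one pair is 99.1% at 0.05 / 3, 97.3% at 0.005 and 91% at 0.00083.

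**The case against.** The article does rank its questions. It names one primary concept, sizes on the NRS alone and places the six- and 12-month effects third, which points to the NRS at the end of treatment. The Bonferroni scope is undefined rather than shown to fail, and a statistical analysis plan that is not shown may state it. This stands in part. But the article asserts the 5% property itself and itself places PPT under the primary heading, so the conflict lies in the published text.

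Four stronger readings are tempting, and the article does not support them.

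- *A frequency could be called dominant at well above 5% error.* The 17–21% counts any of the 10 pairs, and seven of those cannot make a frequency dominant. EA pairs alone reach 6–8%, and for the NRS alone they stay below 5%. If dominant means beating both other EA arms at the same look, the simulated rate is only about 0.2–0.5%.
- *The frequency question has no defined test.* The mixed model with Bonferroni pairs includes the low, high and alternating frequency arms. What is missing is the link to a contrast, endpoint and time.
- *Five PPT sites are five further primary endpoints, giving up to 60% error.* The article calls one site a control and mentions a mean; nothing calls for five separate primary tests. The 60% (1 − 0.95¹⁸ = 60.3%) also assumes independent sites within a person. With an assumed between-site correlation of 0.8 the figure is about 31–37%.
- *Correcting for 10 pairs wastes power.* At the stated difference and SD, power at 0.005 is 97%. A material loss appears only with inputs the article does not give, such as a larger SD or a smaller difference between frequencies.

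**Conclusion.** The concern holds in a limited form. The 5% claim is not supported, because the correction has no stated family while two instruments and three times are left open as primary. Under the usual within-outcome, within-time correction, the chance of any false-positive pair is roughly two to four times the claimed 5%: 10–11% for the NRS over three times and 17–21% with one PPT value added. For the EA-versus-EA pairs the excess is small (6–8%) or absent (3–4%). The simulated figures rest on the assumed correlations and on that reading of the post hoc test. The upper limits in step 3 of the working need only the latter. What makes the point worth correcting is that the present text leaves open which result counts as a positive trial.

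**What to change.** 1. In Outcome measures and Primary outcomes, name the NRS at the end of treatment (week 5) as the single primary endpoint. This fits the named primary concept, the NRS-based sample size and the third rank given to long-term effects.
2. Move PPT and the six- and 12-month NRS to secondary, and state how the PPT sites are combined.
3. In Statistical analysis, define the primary family as the three EA-versus-EA contrasts with family-wise control at 5%. Bonferroni over three (0.0167 each), Holm or a closed test would all serve; the choice is one of preference.
4. Make EA versus control and EA versus placebo a second, separately defined family.
5. Replace the overall claim with one limited to the primary family.

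The cost is wording in two or three sections, with no change to sample size or data collection. The real downside is that PPT or a late time point alone could no longer make the trial positive. The change should be made and dated before anyone sees outcome data by arm.

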### Ethics and data security

All the patients will participate voluntarily and will sign a consent form before randomization. The access and storage of the data will be in accordance with the guidelines of the National Research Ethics Commission (CONEP). This study has been approved by the Ethics Committee of the University of São Paulo Medical School (authorization No. 2.903.991) and in ClinicalTrials.gov under number NCT03802045.

### Auditing

Data may be subject to audits, independent ethics committee (IEC)/Institutional Review Board (IRB) review and regulatory inspection(s). Local investigators will provide direct access to the source data documents.

## Results

This trial still has no results, since it is in the recruitment phase.

## SPIRIT

This protocol has been written in accordance with the Standard Protocol Items: Recommendations for Interventional Trials (SPIRIT) guidelines. The SPIRIT checklist is in Additional file 1.

## Discussion

Although acupuncture, both manual and electrical, is increasingly used to treat LBP, recent studies have concluded that its efficacy still needs to be established [32–35]. Discrepancies in its application and the low methodological quality of the studies produce inconsistent results and lead to it not being recommended according to the current clinical practice guidelines for patients with non-specific LBP [10, 32, 35]. Thus, with no guidance regarding the parameters used, the effect of EA on LBP remains controversial and requires more studies, especially in the older adult population, who are the leading population for this painful condition.

Therefore, there is a need for randomized, controlled, and well-delineated clinical trials in order to standardize EA treatment in LPB and to improve the level of scientific evidence. Here we describe the protocol for a clinical RCT to investigate the efficacy of different frequencies of EA for the treatment of older adults with chronic LBP, and thus to determine the most effective EA frequency.

We expect that the results of this study will aid in the standardization of the technique and provide convincing experimental evidence of the efficacy of EA treatment in older people with LBP.

Our study presents the non-blindness of the practitioner as a limitation, since it is not possible to blind the acupuncturist to the type of treatment.

